### Sample size calculations:

**Attenuated rate of total WMH progression (Table 8):** The sample size calculation is based upon the information obtained from Oregon Brain Aging Study. Assuming a 40% reduction in WMH progression over 3 years among the active group, we would have 80% power to detect this difference with a sample size of 50 subjects per arm at  $\alpha = 0.05$  (two-tailed). Given that we may have 50% reduction in WMH progression over this period, we would achieve 80% power to detect this difference with a sample size of 32 subjects per arm at  $\alpha=0.05$  (two tailed). Thus, with a conservative estimate of about 30% attrition over 3 years, we will achieve at least 80% power to detect reasonable effect size (40%) with a sample size of 150 subjects at baseline.

| Table 8. Sample size calculations for mean change in WMH progression over 3 years* |                    |                                                  |                               |                            |                               |
|------------------------------------------------------------------------------------|--------------------|--------------------------------------------------|-------------------------------|----------------------------|-------------------------------|
| Power
0.80                                                                      | Effect
size (%) | Difference in change
between pufa and placebo | Placebo:
Mean (SD) changes | PUFA: Mean (SD)
changes | Sample size
needed per arm |
|                                                                                    | 40                 | 2.8                                              | 7.0 (5.0)                     | 4.2 (5.0)                  | 50                            |
|                                                                                    | 50                 | 3.5                                              | 7.0 (5.0)                     | 3.5 (5.0)                  | 32                            |

\*Derived from Oregon Brain Aging Study cohort data in participants age 80 and older with total WMH volume  $\geq 6$  cm^3

**Slowed rate of plasma ICAM increase:** Our preliminary data demonstrates that the mean plasma ICAM in non-demented participants of the OBAS under the age of 80 and those age 80 and older were 219.19 ng/mL (SD 39.12) and 269.34 ng/mL (SD 78.89), respectively. We expect that in our trial population (all age 75 and older) a reduction of plasma sICAM-1 in the active group will achieve plasma pufa levels of that observed in the younger participants of OBAS (<80 years old). Under this scenario, we would have over 97% power to detect a reduction in plasma ICAM of this magnitude with the proposed sample  $n=50$  for each arm (i.e., about 52 each at the end of the 3rd year assessment and after 30% drop out with 150 enrolled at baseline).

**Slowed rate of Trails B and Digit Symbol change:** This exploratory aim assumes an annual rate of change in Trails B of 4 seconds and Digit Symbol score of 0.75 in subjects 80 and older (derived from OBAS data) and a total 3-year change of 12 ( $\pm 13$ ) and 2.25 ( $\pm 2$ ), respectively. With 50 subjects in each arm at the end of 3 years follow-up, we would have 80% power to detect the standardized effect size of 0.6 (for example, trails b change

scores: 12 (placebo) vs. 4.7 (active), digit symbol: 2.3 (placebo) vs. 1.1 (active). The distribution of changes in neuropsychological test scores obtained in this pilot trial will provide the basis for the future larger study.

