| Table 5. Plasma ICAM-1 associated with accelerated WMH progression in ADNI**                                                                                     |           |                          |      |                         |       |
|------------------------------------------------------------------------------------------------------------------------------------------------------------------|-----------|--------------------------|------|-------------------------|-------|
|                                                                                                                                                                  | Predictor | Baseline WMH (Intercept) |      | WMH progression (Slope) |       |
|                                                                                                                                                                  |           | $\beta$ (SE)             | P    | $\beta$ (SE)            | P     |
| 1                                                                                                                                                                | ICAM-1    | -0.568 (0.491)           | 0.25 | 0.013 (0.004)           | 0.001 |
| Mixed effects models adjusted for baseline plasma ICAM and total intracranial volume, **Alzheimer's Disease Neuroimaging Initiative, AD subjects excluded, n=404 |           |                          |      |                         |       |

associated with a modest 0.3 ng/mL decrease in plasma ICAM-1 ( $p = 0.02$ , figure 4A). Plasma EPA appears the most significant to plasma ICAM-1 (figure 4B).

increase in plasma PUFA index (EPA+DHA) is

**Study 3 and 4 results suggest that endothelial dysfunction is a risk factor for cognitive decline and white matter disease, and raise the possibility that pufas modulate cerebrovascular function by a mechanism involving ICAM-1**

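### The power of over 97% stated for ICAM-1 takes an age-group contrast as the treatment effect, needs a halved SD on active to reproduce, and sits badly with enrolment from age 75

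*Protocol*

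**What the plan says.** The ICAM-1 paragraph of Sample size calculations gives OBAS means for participants "under the age of 80 and those age 80 and older were 219.19 ng/mL (SD 39.12) and 269.34 ng/mL (SD 78.89), respectively". It then sets the effect by supposing that supplementation "will achieve plasma pufa levels of that observed in the younger participants of OBAS (<80 years old"). The sentence names pufa levels, but the power statement that follows concerns ICAM, so the intended target appears to be the younger group's ICAM-1 level. The result is "Under this scenario, we would have over 97% power to detect a reduction in plasma ICAM of this magnitude with the proposed sample" of 50 per arm, with about 52 expected at year 3 after 30% dropout from 150. The paragraph names neither the SD nor the alpha behind the figure.

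Three other places bear on it. Inclusion Criteria admit participants from age 75. Table 1 gives ICAM-1 in the whole OBAS sample of 86 as 250.5 (SD 74.3). Analytic approach makes the between-arm difference in time slopes the quantity of interest, and the ICAM paragraph is itself headed as a slowed rate of increase. Overall Objective gives Aim 2 a primary hypothesis of its own, on ICAM-1.

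**The concern.** A difference between older and younger people is not evidence of what supplementation does to older people, and nothing in the paragraph links the two. Using the younger group's SD for the active arm would add a second assumption: that treatment halves the spread between people. The age range adds a third difficulty. Participants aged 75-79 belong to the stratum whose mean is the treatment target, so the full 50.15 ng/mL gap may not be available in the enrolled population.

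Aim 2 tests the proposed endothelial mechanism. Set against a stated power of 97%, a non-significant ICAM-1 result could be read as stronger evidence against that mechanism than the design supports.

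**Working it through.** **Inputs.** Means and SDs 219.19 (39.12) and 269.34 (78.89), and n = 50 per arm, from Sample size calculations. Overall OBAS mean 250.5 (SD 74.3) from Table 1. Two-sided alpha 0.05 is stated for WMH and assumed for ICAM-1. Difference: 269.34 − 219.19 = 50.15 ng/mL.

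**Formula.** Power ≈ Φ(δ / √((s₁² + s₂²)/n) − 1.96). The powers below use the corresponding noncentral t (Welch) and differ from this by about a point or less.

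**1. The stated figure.** With 39.12 on active and 78.89 on placebo, the standard error is √((39.12² + 78.89²)/50) = 12.45 and 50.15/12.45 = 4.03. Power is 97.8% (98.1% by the normal formula), so the stated figure reproduces.

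**2. One SD in both arms, δ = 50.15, n = 50.**

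| Common SD | Power |
|---|---|
| 78.89 | 88.2% |
| 74.3 | 91.6% |
| 39.12 | about 100% |

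None of these would naturally be written as over 97%. A common SD of 78.89 with 75 per arm gives 97.2%, but that ignores dropout and contradicts the stated 50.

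**3. Age mix.** Let p be the share aged 75-79 (assumption), and suppose those participants already resemble the under-80 stratum and gain nothing (assumption). Then δ = 50.15(1 − p), and the placebo variance is (1 − p)·78.89² + p·39.12² + p(1 − p)·50.15².

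| p | δ (ng/mL) | Placebo SD | Power, common SD | Power, 39.12 on active |
|---|---|---|---|---|
| 20% | 40.1 | 75.4 | 75% | 91% |
| 30% | 35.1 | 73.1 | 66% | 84% |
| 37.6% | 31.3 | 71.1 | 59% | 77% |
| 50% | 25.1 | 67.1 | 46% | 62% |

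The 37.6% row is the share under 80 that the OBAS means imply: (269.34 − 250.5)/50.15.

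**4. Change instead of level.** The SD of change is 78.89·√(2(1 − ρ)), where ρ is the correlation between baseline and follow-up. The protocol gives no ρ, so the values are assumptions.

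| ρ | SD of change | Power, δ = 50.15 | Power, δ = 31.3 |
|---|---|---|---|
| 0.3 | 93.3 | 76% | 38% |
| 0.5 | 78.9 | 88% | 50% |
| 0.7 | 61.1 | 98% | 72% |

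**5. Detectable difference with 80% power at 52 per arm.** (1.96 + 0.8416)·SD·√(2/52) is 43.3 ng/mL for SD 78.89 and 40.8 ng/mL for SD 74.3.

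**The case against.** The strongest reply is that the sum is right and openly conditional: it follows from the scenario as described, and the use of the under-80 SD is inferred rather than stated. That stands. The fault lies in the inputs and not in the arithmetic.

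Second, ICAM-1 is measured at baseline and at seven follow-up visits and analysed longitudinally, so a single cross-sectional SD may understate power. This stands in part. At ρ = 0.7 a change analysis recovers 98% for 50.15 ng/mL and cancels the SD point. It does not support the effect size itself. At 31.3 ng/mL the SD of change would have to fall to 31.31/(0.2 × (1.96 + 1.88)) = 40.8 for 97% power, a correlation of about 0.87, and the protocol reports none.

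Third, the age-mix powers depend on an assumed share, and on 75-79-year-olds resembling unselected OBAS participants under 80. Entry requires WMH of at least 5 cc and low plasma PUFA, and the Significance section cites one study with higher sICAM-1 at greater WMH grade (and another without). So the documents do not show that the placebo mean must fall below 269.34. The mixture figures show sensitivity and are not estimates.

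A reader might also infer that the protocol's own regression refutes the 50 ng/mL effect, because each 100 ug/mL of PUFA index is "associated with a modest 0.3 ng/mL decrease in plasma ICAM-1". The documents do not support that inference. With the Table 1 SDs (26.7 and 74.3) and n = 86, that slope gives r = −0.003 × 26.7/74.3 = −0.001 and p = 0.99 unadjusted, against the printed p = 0.02. A slope that fits p = 0.02 would be near 0.7 ng/mL per ug/mL. Over an assumed rise of 85 ug/mL that is about 59 ng/mL, which is more than the assumed effect. The coefficient is doubtful as printed, and no power should be quoted from it.

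**Conclusion.** The point holds in limited form. The stated power of over 97% is not supported by the trial's design. It depends on an age contrast standing in for a treatment effect, apparently on a halved SD in the active arm, and on a reference stratum that overlaps the enrolled age range. The SD alone costs about 6 to 10 points (97.8% to 92% or 88%). The effect size and age mix could cost considerably more, on assumptions that the protocol neither gives nor excludes. The calculation also uses cross-sectional means where the analysis concerns change.

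It does not follow that Aim 2 is known to be underpowered: without an SD of change, the true power cannot be fixed. Nor is the trial's size in question, since 150 rests on WMH.

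A reader might extend the criticism to Aim 3, where the same section says "we would have 80% power to detect the standardized effect size of 0.6". A Trails B change SD of 13 against the Table 1 SD of 77 implies a correlation of 1 − 13²/(2 × 77²) = 0.986 if the variance is stable. That warrants checking the 13. It does not yield a power figure, because the Trails B assumptions are drawn from participants aged 80 and older while Table 1 covers all 86, and Aim 3 is already labelled exploratory.

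**What to change.** Remove the 97% claim. State instead the ICAM-1 difference detectable with 80% power at about 52 per arm, using one SD for both arms from OBAS participants aged 75 and older. Where OBAS holds repeat ICAM-1 values, use the SD of change, so that the calculation matches the analysis of change and slopes. On the cross-sectional SDs now in the protocol the detectable difference is roughly 41-43 ng/mL. Name the SD and alpha used, and correct the sentence that gives a pufa level as the ICAM-1 target.

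Separately, reconcile the coefficient and p-value printed in Study 4 with Table 1 before citing them for any effect size, and check the Trails B change SD of 13 against its source.

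The cost is a text change and a re-run of data already held. The stated power for Aim 2 becomes less favourable. Sample size, visits and conduct do not change.

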| Clinical Dementia Rating of 0, No./Total (%)               | 60/86 (70)     |
| Years of follow-up, mean (min/max)                         | 4.0 (1/6)      |
| Plasma biomarkers                                   |                |
| PUFA index (EPA+DHA), ug/mL                                | 84.5 (26.7)    |
| Eicosapentaenoic acid (EPA, 20:5n-3), ug/ml                | 16.5 (10.5)    |
| Docosahexaenoic acid (DHA, 22:6n-3), ug/ml                 | 68.1 (17.8)    |
| ICAM-1, ng/ml                                              | 250.5 (74.3)   |
| Cognitive profile                                   |                |
| MMSE                                                       | 28 (2)         |
| Trail Making Test Part B                                   | 137 (77)       |
| Digit Symbol Making Test                                   | 39 (13)        |
| Delayed paragraph recall                       | 14.0 (4.7)     |
| Brain MRI profile                                   |                |
| n=32                                                |                |
| Total Intracranial Volume, cm                  | 1107.5 (106.4) |
| Total Brain Volume, cm                         | 821.1 (84.7)   |
| Total Ventricular Volume, cm                   | 55.2 (16.5)    |
| White matter hyperintensity (WMH), cm          | 13.8 (8.8)     |
| Mean and standard deviation unless otherwise stated        |                |
|  WMS-R logical memory-delayed paragraph recall |                |

| Table 2. PUFA index (EPA+DHA) is associated with less executive decline in non-demented elders over 4-years follow up |                  |                               |      |                           |      |
|-----------------------------------------------------------------------------------------------------------------------|------------------|-------------------------------|------|---------------------------|------|
|                                                                                                                       |                  | Baseline function (Intercept) |      | Cognitive decline (Slope) |      |
|                                                                                                                       |                  | $\beta$ (SE)                  | P    | $\beta$ (SE)              | P    |

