**Statistical Analysis:** **Aim 1: Determine pufa effects on WMH accumulation over 3 years in non-demented elders, age  $\geq 75$  with low plasma pufa status and WMH burden at entry.** This aim will test the hypothesis that pufas slow WMH accumulation compared to the placebo. **Aim 2: Determine pufa effects on biomarkers of endothelial function.** This aim will test the hypothesis that pufas improve plasma measures of endothelial function. **Aim 3: Determine pufa effects on cognitive change.** This aim tests the hypothesis that pufas slow the executive function and processing speed decline, an effect mediated by WMH.

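### The Aim 3 detectable differences on Trails B and Digit Symbol rest on 3-year change SDs that the protocol's own cohort table makes hard to credit

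*Protocol*

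**What the plan says.** The protocol's sample size section, under the paragraph on Trails B and Digit Symbol, takes annual changes of 4 s and 0.75 points from OBAS participants aged 80 and older. It gives 3-year totals of "12 ( $\pm 13$ ) and 2.25 ( $\pm 2$ ), respectively". It then puts 50 participants per arm at year 3 into the calculation and concludes: "we would have 80% power to detect the standardized effect size of 0.6". The worked examples are "12 (placebo) vs. 4.7 (active), digit symbol: 2.3 (placebo) vs. 1.1 (active".

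Table 1 in the Approach section describes 86 non-demented OBAS participants with mean age 85.7. Its row for "Trail Making Test Part B" reads 137 (77), and the Digit Symbol row reads 39 (13). The footnote says the bracketed values are standard deviations unless stated otherwise.

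The protocol calls Aim 3 exploratory. The Statistical Analysis section lists a t-test on changes as a descriptive step, followed by a linear mixed model over baseline and months 12, 24 and 36.

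**The concern.** The assumed SD of 3-year change is about one sixth of the between-person SD in the same cohort (13 against 77 s, 2 against 13 points). A change SD that small means people keep almost exactly their position relative to one another for three years. That would be unusually high stability for a timed test at this age, and the protocol offers no data to support it.

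The standardized statement does not depend on the SD, but its translation into seconds and points does. If the SDs are too small, readers will believe the trial can see a 7.3 s or 1.2-point difference when it may be able to see only much larger ones, and they may take a null cognitive result as more informative than it is.

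**Working it through.** **Inputs.** 50 per arm; change SDs 13 s and 2 points; examples 12 vs 4.7 and 2.3 vs 1.1 (all from the sample size section). Baseline SDs 77 s and 13 points (Table 1). Two-sided alpha of 0.05 is stated for Aim 1 and assumed here for Aim 3. The ± values are read as SDs, because only then do the examples give effect sizes near 0.6.

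**1. The plan's own figure.**
- Normal approximation: power = Φ(d × √(50/2) − 1.96). With d = 0.6 this is Φ(3.00 − 1.96) = Φ(1.04) = 85.1%; the noncentral t gives 84.4%.
- The d that has 80% power at 50 per arm is 0.560 (normal) or 0.566 (t).
- Trails B example: 7.3/13 = 0.56, power 80.2% (normal) or 79.4% (t).
- Applying d = 0.56 to both tests returns the printed examples: 12 − 0.56 × 13 = 4.72, printed 4.7; 2.25 − 0.56 × 2 = 1.13, printed 1.1.
- So 0.6 is 0.56 shown to one decimal. It slightly understates power.

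**2. Correlation implied by the SDs.** With s1 and s2 the SDs at baseline and year 3, SDchange² = s1² + s2² − 2·r·s1·s2.
- Equal SDs: r = 1 − SDchange²/(2·s1²). Trails B: 1 − 169/11,858 = 0.986. Digit Symbol: 1 − 4/338 = 0.988.
- Smallest r over every possible s2: √(1 − SDchange²/s1²). Trails B: √(1 − 169/5,929) = 0.986. Digit Symbol: √(1 − 4/169) = 0.988. The result therefore does not need equal variances.
- If the baseline SDs were only half of Table 1 (38.5 s and 6.5 points), the smallest r would still be √(1 − 169/1,482.25) = 0.94 and √(1 − 4/42.25) = 0.95.

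**3. What other correlations would mean.** The protocol gives none, so these values of r are assumptions. SDchange = s1 × √(2(1 − r)). Power is by noncentral t for 7.3 s and 1.2 points, and the detectable difference is 0.566 × SDchange.

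| r | Trails B change SD | Power for 7.3 s | Detectable at 80% | Digit Symbol change SD | Power for 1.2 points | Detectable at 80% |
|---|---|---|---|---|---|---|
| 0.70 | 59.6 s | 9% | 34 s | 10.1 | 9% | 5.7 |
| 0.80 | 48.7 s | 12% | 28 s | 8.2 | 11% | 4.7 |
| 0.90 | 34.4 s | 18% | 19 s | 5.8 | 18% | 3.3 |
| 0.95 | 24.3 s | 32% | 14 s | 4.1 | 30% | 2.3 |

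At r = 0.95 the detectable differences are 13.8 s and 2.33 points. Both exceed the whole assumed placebo decline of 12 s and 2.25 points, so for r of 0.95 or less even complete arrest of decline would have under 80% power on a change score. Above that the picture eases: at r = 0.97, power for the two examples is 48% and 46%.

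**The case against.** The strongest reply is that the statement concerns a standardized effect. Fifty per arm gives 80% power at d of about 0.57 whatever the SD, and the seconds and points are only examples. That stands, so it would be wrong to conclude that the 80% figure itself is false. Only its translation into test units is in doubt.

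Several further limits also stand:
- Table 1 covers the whole cohort, while the change rates are for those aged 80 and older. Halving the baseline SDs still leaves r at 0.94 or more, so this softens the point without removing it.
- The documents report no test-retest correlation. They do not show where the 13 and 2 came from; that they are SDs of model-fitted slopes is possible but unproven.
- The table in the working is for a two-point change score. The mixed model over four visits may gain some precision, though the protocol computed its power on 3-year change.
- Aim 3 is exploratory and does not set the sample size.

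A reader might be tempted by three stronger readings, none of which the protocol supports:
- *An arithmetic error in the power.* The gap between 84% and 80% is rounding of 0.56, and it is conservative.
- *A clash with Aim 1.* The examples imply slowing of 61% (7.3/12) and 52% (1.2/2.3), beside "Assuming a 40% reduction in WMH progression over 3 years among the active group" and a cognitive effect described as "an effect mediated by WMH". But mediation does not make percentage slowing of cognition equal to, or capped by, percentage slowing of lesion growth. The examples show what is detectable, not what is expected, and Table 8 also carries a 50% scenario. The protocol's own preliminary estimate, 4 s per year on Trails B per 100 ug/ml of PUFA index, would allow a large effect.
- *Doubtful SDs passed on to a later trial.* The protocol says the follow-on study will rest on the score changes observed in this trial, not on these assumed SDs.

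**Conclusion.** The concern holds in a limited form. The change SDs of 13 s and 2 points are compatible with Table 1 only if the 3-year correlations are at least about 0.99 (about 0.94 to 0.95 if the true baseline SDs are half those shown). The protocol's cohort data therefore do not support detectable differences of 7.3 s and about 1.2 points at 80% power. How far off they are cannot be fixed from the document. Over an assumed correlation range of 0.7 to 0.95, power for the quoted examples is about 9% to 32% on two-point change scores.

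The conclusion rests on reading the ± values as SDs, on Table 1 being a fair guide to participants aged 80 and older, and on two-sided alpha of 0.05. The primary outcome and the sample size are unaffected.

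**What to change.** 1. Compute the SD of observed 3-year change in Trails B and Digit Symbol in OBAS participants aged 80 and older, and compare it with 13 s and 2 points. Replace these values if they prove to be model-based or otherwise not SDs of observed change.
2. Restate the detectable differences in seconds and points on the verified SDs. If those SDs show it, say plainly that this exploratory aim does not have 80% power for the examples now quoted.
3. As a minor correction, print the effect size as 0.57 (t-test) or 0.56 (normal approximation) in place of 0.6, which has 84% power.

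The cost is a short recomputation from the cohort data on which the protocol already draws. The downside is that the stated detectable differences are likely to become less favourable. No additional participants are needed.
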